### Process evaluation: Feasibility

In the first part of the process evaluation we will evaluate the feasibility of the intervention, and describe 1) user data, 2) participation in and evaluation of the training, 3) physician and patient satisfaction and acceptance of the CDSS and patient portal. These descriptive statistics will be presented as percentages or means with standard deviations.

### Process evaluation: Shared decision making

Differences in mean change between arms will be analyzed with the use of multi-level modelling and will be expressed as mean differences with 95% CIs. We will analyze differences in perceived SDM and observed SDM for both patients and physicians in the intervention and control groups. Finally, we will assess the differences between the intervention and control groups on recall (NPIRQ), adherence (pharmacy records), and quality of life (EQ-5D-5L).

### Per protocol analysis

Logged data by the CDSS and patient portal will be used to select participants for a per protocol analysis for the primary outcome. In this analysis, we will only include patients from the experimental group that meet the following two criteria 1) physicians used the CDSS in the consult with the patients and 2) physician used the ‘print’ button in the CDSS or the patient visited the patient portal at least once after the consultation.

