### Process evaluation: Feasibility

To assess the feasibility of the intervention, we will collect the following: 1) data logged by the CDSS and patient portal, 2) participation data of the CDSS training, 3) physician satisfaction regarding the CDSS, 4) the Technology Acceptance Model (TAM; [61]) questionnaire; 5) the Website Satisfaction Scale questionnaire (WSS [62]), 6) videotaped consultations, 7) pharmacy records, and 8) falls calendar entries.

Usage data of the CDSS and patient portal will be measured throughout the study period. The extent to which the intervention was implemented as intended (fidelity/dose delivered) and the extent to which the participants actively engage with the intervention (dose received/exposure) will be assessed through data logged by the CDSS and patient portal, and the videotaped consultations. Dose received/exposure will also be assessed through participation data of the CDSS training. Reach/participation rate will be assessed through data logged by the CDSS to analyze the extent to which physicians propose changes in FRID prescriptions. Patients will be asked to self-report changes in medication use on the fall calendar on a weekly basis. These falls calendar entries and pharmacy records will be used to analyze the extent to which patients adhere to the physicians’ advice and changes in the treatment plan. Satisfaction with the intervention (dose received/exposure) will be measured through physician evaluations of the CDSS and the WSS questionnaire (patients). The TAM questionnaire assesses the perceived usefulness, perceived ease of use, and intended usage of the CDSS, and the WSS measures the comprehensibility, satisfaction and Emotional Support of the patient portal [62]. Finally, barriers and facilitators (context) will be assessed through the videotaped consultations, and physician evaluations of the CDSS by means of a survey.

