### Estimating the effectiveness of the intervention on trial outcomes

For every participant, we will assess fall incidents during a fixed follow-up period of 12 months, which will start after a set 1 month, during which the dose of FRIDs will be stopped or decreased. Difference in time to injurious fall between the intervention and control group in the follow-up period will be analyzed by means of a multilevel Cox regression model based on hospital level [69]. Model fit will be assessed using standard approaches (e.g., the proportional hazards assumption with Schoenfeld residuals). We will adjust all models for age, sex and type of hospital, i.e. academic versus non-academic. In a sensitivity analysis, we will additionally adjust for significant baseline differences. Difference in total number of (injurious) falls in the follow-up period between the control and intervention groups will be analyzed by means of multilevel Poisson regression models based on hospital level. In the case of overdispersion, we will apply either quasi-Poisson regression or negative binomial regression depending on the observed distribution of the data. Difference between the intervention and control group with respect to time to any fall and time to fall that results in any injuries will be analyzed by means of survival analyses, similarly to the primary outcome.

Differences in EQ-5D-5L index score, EQ-5D visual analogue scale, and TOPICS-SF summary score between the intervention and control group after 12 months will be analyzed by means of linear mixed models. These models will be adjusted for the baseline value of the outcome [70].

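### The per-protocol rule lets a portal visit at any time, even after a fall, qualify an intervention patient, so its hazard ratio can differ from 1 with no treatment effect

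*Protocol article*

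**What the plan says.** The protocol article, section Per protocol analysis, states that logged CDSS and portal data "will be used to select participants for a per protocol analysis for the primary outcome". The rule is specific: "we will only include patients from the experimental group that meet the following two criteria". The first criterion is that "physicians used the CDSS in the consult with the patients". The second is met in either of two ways: "physician used the ‘print’ button in the CDSS", or "the patient visited the patient portal at least once after the consultation". No period is set for that visit, and no rule is given for control patients.

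Three other places bear on it.

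- Process evaluation: Feasibility: "Usage data of the CDSS and patient portal will be measured throughout the study period". The logs would therefore record a visit late in follow-up, and such a visit meets the criterion as worded.
- Statistical analysis, trial outcomes: the 12-month outcome window is described as one "which will start after a set 1 month, during which the dose of FRIDs will be stopped or decreased". So there is a defined month between the consultation and the start of the outcome clock.
- The same section adjusts the models for age, sex and type of hospital, and the Statistical analysis section makes intention to treat the principle for the trial data.

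**The concern.** Membership of the per-protocol set can be decided by something that happens inside the outcome window. This can bias the comparison in two ways.

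1. **Time.** If an injurious fall changes how likely a patient is to open the portal afterwards, the outcome itself helps decide who is counted. Fewer visits after a fall would remove patients with events from the intervention side. More visits after a fall would add them.
2. **Prognosis.** Patients who open the portal may differ in fall risk from those who do not. The intervention side is filtered on this and the control side is not. Adjustment for age, sex and hospital type removes only the part of the difference that those variables carry.

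This is the only per-protocol analysis described, and it concerns the primary outcome. As written, it cannot separate an effect of using the tools from the way users were selected.

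**Working it through.** **The plan's own figure.** The protocol gives no number for the per-protocol analysis. The Sample size section supplies the control risk of 0.22, and its figures reproduce: (1.96 + 0.8416)² × (0.22×0.78 + 0.12×0.88) / 0.10² = 217.6 per arm. The design effect is 1 + 76×0.01 = 1.76, which gives 382.9 against the stated 385. Then 770/0.9 = 855.6, so 856.

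**Assumptions.** The protocol gives neither a print rate nor a visit rate. I take a true null with 12-month risk 0.22 in both arms, all controls kept, and the CDSS used in every consult. Falls count from month 1 to month 13. Visits occur at a constant rate such that 50% would visit by month 13 without a fall. The print probability *p* and the ratio *f* of visit rate after to before a first injurious fall are varied.

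**A. Time-related part.**

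- Fall hazard: λ = −ln(0.78)/12 = 0.02071 per month.
- Visit rate: μ = −ln(0.5)/13 = 0.05332 per month.
- Chance of a visit by month 13 for a patient who falls *t* months into follow-up: v(t) = 1 − exp[−μ(1+t) − fμ(12−t)].
- Inclusion probability: w(t) = p + (1−p)v(t) for fallers, and w₀ = p + (1−p)×0.5 for non-fallers.
- Events: E = ∫₀¹² λe^(−λt) w(t) dt. Person-time: P = ∫₀¹² tλe^(−λt) w(t) dt + 12×0.78×w₀.
- Hazard ratio against controls, taken as a ratio of event rates: (E/P)/λ.

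Example with f = 0 and p = 0: E = 0.0639 and P = 5.146 months, so E/P = 0.01242 and the ratio is 0.01242/0.02071 = 0.60.

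| Visit rate after a fall | No prints | 50% prints | 75% prints |
|---|---|---|---|
| Stops (f = 0) | 0.600 | 0.869 | 0.944 |
| Halves (f = 0.5) | 0.826 | 0.942 | 0.975 |
| Unchanged (f = 1) | 1.000 | 1.000 | 1.000 |
| Doubles (f = 2) | 1.243 | 1.082 | 1.035 |

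**B. Prognosis part, taken separately.** Half of patients are visitors, with 0.75 times the risk of non-visitors. Non-visitor risk = 0.22/(0.5×0.75 + 0.5) = 0.2514, and visitor risk = 0.1886.

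- No prints: ln(1 − 0.1886)/ln(0.78) = 0.84.
- 50% prints: included risk = (0.5×0.1886 + 0.25×0.2514)/0.75 = 0.2095; hazard ratio 0.95.
- 90% prints: included risk = (0.5×0.1886 + 0.45×0.2514)/0.95 = 0.2183; hazard ratio 0.99.

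For the chance of a falsely significant benefit, I compare proportions with 385 controls and 385 × the included fraction, variance multiplied by 1.76.

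- No prints: difference 0.0314, standard error 0.0467, chance 9.9%.
- 50% prints: difference 0.0105, standard error 0.0424, chance 4.3%.

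The nominal figure is 2.5%.

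**C. Check of the remedy.** If only visits before month 1 count, v = 1 − exp(−μ) for everyone, whatever happens later. Inclusion no longer depends on *t*, w cancels from E and P, and the time-related hazard ratio is exactly 1.00. Part B is not removed.

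**The case against.** Several points on the other side are sound.

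- **Direction.** A reader might infer that the bias most likely favours the intervention. The documents do not support that for the time-related part. An injurious fall does not end portal access, and the treatment plan stays available there. Patients with a life expectancy under one year are excluded, so death should rarely cut off the chance to visit. If falls prompt visits, the bias runs against the intervention.
- **Size.** The value 0.60 is an extreme case: no printing, a constant visit rate all year, and no visits after a fall. The print function sits on the CDSS's final screen, and the plan appears in the portal after the consultation, so early visits are plausible. If 80% of visitors log on in month 1 (an assumption), with visits still stopping after a fall, the ratios are 0.90, 0.97 and 0.98 for 0%, 50% and 75% prints.
- **The print route.** Print and portal are alternatives, so patient behaviour decides inclusion only where the physician did not print. A high print rate makes both parts small.
- **Controls.** They have no CDSS or portal logs, so the same filter cannot be applied to them. The absence of a matching filter is unavoidable; comparing without adequate adjustment for prognosis is not.
- **Status.** The analysis is supplementary to an intention-to-treat analysis.

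It could also be said that a full analysis plan may add a visit window. But the article states a specific two-part rule, and as worded it admits visits made after the outcome. That defect is on the page and is not an omitted detail.

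**Conclusion.** The point stands as one about a badly fixed rule. Followed as written, the per-protocol analysis can give a hazard ratio away from 1 when the intervention does nothing.

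Under the stated assumptions, the time-related part ranges from 0.60 to 1.24 with no prints and from 0.87 to 1.08 with 50% prints. It is nil if falls do not change visiting. Selection on prognosis at 0.75 times the risk gives 0.84 with no prints, 0.95 with 50% and 0.99 with 90%. These figures show what is possible. They do not predict the result, because the print rate, the visit rate, the timing of visits and the response to a fall are all unknown.

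Two further inferences should be resisted. The primary result is not compromised, because the intention-to-treat analysis does not use this rule. Nor does the point call for a complier-average analysis with hospital allocation as instrument. Intervention patients receive the question prompt list and pre-visit portal content, and their physicians are trained, whether or not they meet the per-protocol criteria. Allocation can therefore act outside the defined adherence. In addition, two of the ten hospitals were placed in their arms by default.

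The rule should be corrected before analysis.

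**What to change.** 1. Define per-protocol status only from actions completed before the outcome clock starts: CDSS used in the consult, and either the summary printed or the portal visited within the set 1-month period before follow-up. This removes the time-related part.
2. Adjust the restricted comparison for baseline fall risk, using the prediction-model variables that the Data management section already has extracted from the patient record for both arms. This reduces the prognosis part but cannot be assumed to remove it.
3. State that all controls are kept, and label the result a non-randomised, supplementary comparison.

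The cost is a few sentences and extra covariates in one model; the logs and variables are already collected. Patients whose only qualifying action is a late portal visit leave the set. They are few if printing is common or visits cluster soon after the consultation. They are more if neither holds: at the constant rate assumed above, only 1 − exp(−0.0533) = 5% of patients would have visited by month 1. The print rate and visit timing can be tabulated from the logs, without reference to outcomes, before the rule is finalised.

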### Sample size

Sample sizes of *n* = 385 in the intervention and *n* = 385 in the control group (10 clusters with 77 patients in each cluster) are needed to detect a difference in proportion of injurious falls of 0.10 with 80% power. We inferred the proportion of patients who will experience an injurious fall to be 0.22 in the control and 0.12 in the intervention group. In these calculations, we assumed the two-sided significance level of 5% and an intraclass correlation coefficient of 0.01 to account for clustering [71]. Presupposing a drop-out rate of 10%, 856 patients will need to be included.

### Monitoring

A data monitoring committee will not be established since the overall risk associated with the trial is considered negligible.

### Harms

All adverse events and serious adverse events reported by the subject or observed by the researchers or his staff will be recorded in an electronic database. Serious adverse events will also be reported to the medical ethics committee of the Amsterdam UMC.

## Discussion

The multicenter RCT described in this paper will assess: a) the effectiveness of the multicomponent intervention (i.e., use of CDSS and patient portal) compared with usual care. Effectiveness will be assessed in terms of time to first injurious fall (primary outcome). As secondary aims, cost-effectiveness and the feasibility of the intervention will be assessed.

The deprescribing of FRIDs requires complex decision making. We expect that the implementation of our CDSS and patient portal, supported by a prediction model and guideline-based advice, will aid in optimizing deprescribing decisions for both the physician and patient, consequently reducing fall risk. In line with the expectation that the intervention will aid in the prevention of injurious falls, it is hypothesized that the intervention will be more cost-effective compared to care-as-usual regarding fall-related health care costs. The direct healthcare and follow-up care resulting from injurious falls among older adults potentially involve 0.85 to 1.5 percent of the total healthcare expenditures in Western countries [13].

The process evaluation will evaluate a) the implementation of the intervention and b) how this intervention leads to enhanced SDM and patient outcomes. A systematic review has suggested that SDM can lead to better affective-cognitive outcomes, e.g. improved satisfaction and less decisional conflict [72]. Thus, we hypothesize that physicians and geriatric patients as well as their caregivers will evaluate the intervention workflow more positively compared to the care-as-usual workflow and will engage in more SDM regarding the patient’s treatment plan. Recent studies have illustrated that compliance to FRID-deprescribing is often poor. In a study by Boyé et al. [73], researchers found that compliance to their intervention of FRIDs-withdrawal was limited among patients. The researchers found that 35 percent of all deprescribing attempts were unsuccessful, either due to non-compliance, recurrence of the initial indication for prescribing, or additional medication being described for newly diagnosed conditions. Moreover, the STRIDE trial, a multicenter randomized controlled trial by Bhasin et al. [74] evaluated a multifactorial intervention that included the use of motivational interviewing to encourage patients to choose recommendations they were willing to address. Among the patients for which medication use was identified as a risk factor, only 29 percent of patients agreed to address this risk. We expect that a higher degree of SDM will lead to more recall and knowledge among patients, leading to more treatment and medication adherence among patients. This in turn, could also lead to less medication-related injurious falls among patients.

An important strength of our study is that we developed the intervention following the MRC guidelines. The aim of the framework is to ensure that feasible interventions are empirically and theoretically founded and that considerations are given both to the effectiveness of the intervention and how it works. The intervention’s end-users are included in each phase of the project. This way, we will be able to optimally personalize the intervention’s design to the heterogeneous needs of the end-users.

Another asset of our study is that it includes both an effect evaluation and a process evaluation. This will help us to not only assess whether the intervention was effective, but the process evaluation will also make it possible to assess whether the intervention was implemented correctly, and which implementation factors were facilitating or impeding. Gaining more insight into the context will deepen our understanding of why the intervention was (not) successful.

The findings of this study will add valuable insights about how digital health informatics tools, based on prediction models, can support SDM between physicians and older adults. This new knowledge will be especially insightful in the case of FRIDs withdrawal among older adults. Furthermore, this study will also contribute to the literature on risk communication, since it investigates how physicians will use a visualized fall-risk estimate in their consultations with the patient.

### Outlook

If the AD*F*ICE_IT intervention will prove to be effective, it could be implemented in routine healthcare practices. The hospitals in the intervention group can continue using the CDSS and patient portal as they have done during the RCT, as the intervention will already be implemented in their electronic patient record systems. The hospitals in the control group could also implement the CDSS and patient portal software at the end of the study. Furthermore, the software will be available as open source to facilitate national and international implementation. We expect that once implemented at the falls clinic of the geriatric departments, the AD*F*ICE_IT intervention will contribute to individualized and cost-effective prevention of (medication-related) injurious falls among older adults.

## Abbreviations

AD*F*ICE_IT: Alerting on adverse Drug reactions: Falls prevention Improvement through developing a Computerized clinical support system: Effectiveness of Individualized medicaTion withdrawal
CDSS: Clinical decision support system
CI: confidence interval
DCS: Decisional Conflict Scale
EQ-5D-5L: EuroQol-5D-5L
FRID: Fall-Risk Increasing Drug
IMCQ: institute for Medical Technology Assessment Productivity Cost Questionnaire Medical Consumption Questionnaire
IPCQ: institute for Medical Technology Assessment Productivity Cost Questionnaire Productivity Cost Questionnaire
MMSE: Mini-Mental State Examination
MOCA: Montreal Cognitive Assessment
MRC: Medical Research Council
NPIRQ: Netherlands Patient Information Recall Questionnaire
PrepDM: Preparation for Decision-making scale
QALY: quality-adjusted life years QPL: Question Prompt List
RCT: Randomized Controlled Trial
SDM: Shared Decision Making
TAM: Technology Acceptance Model
TOPICS-SF: The Older Persons and Informal Caregivers Survey–Short Form
UI: User Interface
WSS: Website Satisfaction Scale
